#### Secondary outcomes

Time to cough resolution: defined as the length of time (day) from treatment start to cough complete resolution.Time to cough relief: defined as the length of time (day) from treatment start to cough relief.Change from baseline in cough symptom score (CSS) at days 7 and 14

CSS is a simple, short, and subjective tool to evaluate the overall frequency and severity of cough in the day and at night. There are daytime (from 8:00 am to 8:00 pm) and nighttime (from 8:00 pm to 8:00 am) CSS, each comprising four possible outcomes with a score range from 0 to 3 points [10]. During the trial, each patient will self-complete and record the CSS in the cough diary every day. Daytime CSS of the last 12 h will be assessed at about 8:00 pm and nighttime CSS of the last 12 h at about 8:00 am. The total CSS is the sum of daytime and nighttime CSS.
4.Change from baseline in TCM syndrome score at days 7 and 14

Each TCM symptom is graded according to TCM symptoms grading criteria (see Additional file 1). Each TCM symptom score of the past 24 h will be evaluated and graded every night at about 8:00 pm during treatment. TCM syndrome score is the sum score of the main and all minor symptoms.
5.Change from baseline in VAS value at days 7 and 146.Change of CQLQ from baseline to post-treatment

Cough-specific quality of life questionnaire (CQLQ) is a valid and reliable tool to evaluate the impact of cough on health-related quality of life [11], consisting of six domains including 28 items. The total score ranges from 28 to 112, with lower score indicating a better quality of life [13].

### Adverse events reporting

Adverse events refer to the unexpected medical events that occur during the study, which may not have a causal relationship with the medication. Events can be symptoms, signs, and laboratory abnormalities. Any adverse event will be recorded and reported according to standard procedures. A SAE will be defined as any medical occurrence that results in death, is life-threatening, requires inpatient hospitalization or prolongation of existing hospitalization, results in persistent or significant disability and/or incapacity, is a congenital anomaly or birth defect, or other important medical events. Other events may be considered as a SAE when the event may jeopardize the patient and may require medical or surgical intervention to prevent one of the following outcomes: death, life-threatening, or hospitalization. SAE must be reported to the Biomedical Ethics Committee of West China Hospital of Sichuan University, the sponsor, and China’s State Food and Drug Administration within 24 h.

### Coordination and conduct of the trial

Three investigator meetings have been held to review the study protocol, informed consent, and data collection form. Additionally, before the start of patient recruitment procedures, all documents and funding required for the study and investigational medications should be fully available. One investigator meeting will be held in each participating site to train all trial-related personnel mainly for patient recruitment and data collection. Data monitoring committee is not needed because (1) this is a relatively short-term trial, (2) the primary and secondary endpoints are solely patients’ self-reported symptoms, and (3) the pilot clinical observation did not show potential for toxicity. Interim efficacy analysis will also be not conducted.

The study will be monitored by an independent monitoring committee. The monitor regularly conducts onsite monitoring and reviews the CRFs to ensure participants’ rights and interests, compliance with the trial protocol, source data validity, data accuracy, and data integrity. The study will be audited randomly by an independent auditor regarding trial conduct and compliance with the protocol, standard operating procedures, good clinical practice, and the applicable regulatory requirements.

### Data collection and management

All data including baseline, outcomes, and other trial data will be collected and recorded timely in the paper CRFs. Measures taken to maximize participant retention are as follows: (1) highlighting the significance of participant’s involvement in the study; (2) making use of all available contact information including phone number(s), e-mail address, QQ and WeChat; (3) reminding participants of the upcoming scheduled visits; (4) acknowledging and complimenting participant’s commitment, time, and effort devoted to the study when they complete scheduled visits; (5) attempting to re-contact/re-schedule within 24 h for missed appointments; (6) providing a compensation of ¥400 after completing follow-up; and (7) trying to obtain the participant’s consent for one last visit to collect outcome data when a participant withdraws from the study.

EpiData3.1 database will be used for data entry and management. To ensure the accuracy of the data, double data entry and proofreading will be performed by two independent data administrators. Any query about CRFs will be issued to the investigators and answers should be returned as soon as possible. The database will be backed up regularly and stored off-site. The primary investigators, data administrators, and biostatisticians will check, confirm, and lock the database prior to data processing. Only data administrators and biostatisticians will have access to the final data. Original CRFs and any other records will be kept on file at each participating site for 5 years.

### Sample size calculation

The sample size was calculated on basis of cough relief rate, using PASS 11.0. Based on the pilot clinical observation of 144 patients with postinfectious cough [8], cough relief rate in active treatments was estimated to 70%, with a difference of 30% or more considering clinically significant. Setting a two-sided *α* of 0.05 and *β* of 0.15, the sample size was estimated to be 46 cases for each group. Additionally, this trial involves exploring the effect and safety of different dosage; the sample size for each group was set to 60 cases. Taking approximate dropouts of 20% into account, the number of participants recruited was estimated to be 72 per group. Therefore, a total of 216 patients will be recruited in this trial.

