**Methods:**

This study is a prospective, multi-center, randomized, double-blinded, parallel group, placebo-controlled trial. A total of 216 adult participants with postinfectious cough will be enrolled from six study centers across China. All participants are randomly allocated to one of three parallel treatment groups: (1) 15 g of active ZHWFG three times daily, (2) 10 g of active ZHWFG plus 5 g of ZHWFG-matched placebo three times daily, and (3) 15 g of ZHWFG-matched placebo three times daily. The treatment duration is 14 consecutive days. The primary outcomes are cough resolution rate and cough relief rate. Secondary outcomes include time to cough resolution, time to cough relief, change from baseline in cough symptom score, cough visual analog scale value, traditional Chinese medicine syndrome score at days 7 and 14, and change of CQLQ from baseline to post-treatment as well as adverse events.

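### The 20% dropout allowance is applied as 60 × 1.20 = 72; keeping 60 per group after 20% loss needs 60 / 0.80 = 75

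*Protocol article*

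**What the plan says.** The section on sample size calculation in the protocol article proceeds in three steps.

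- **Power step.** Cough relief on active treatment is put at 70%, "with a difference of 30% or more considering clinically significant". The result is then given: "Setting a two-sided *α* of 0.05 and *β* of 0.15, the sample size was estimated to be 46 cases for each group".
- **Margin for dose exploration.** Because the trial also explores the effect and safety of different doses, "the sample size for each group was set to 60 cases". No calculation is attached to this increase.
- **Dropout step.** "Taking approximate dropouts of 20% into account, the number of participants recruited was estimated to be 72 per group". Three groups of 72 give 216.

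The total is repeated in the section on patient population and setting and in the abstract: "A total of 216 adult participants with postinfectious cough will be enrolled from six study centers across China". Nowhere does the article give another dropout rate or define the allowance in another way.

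**The concern.** A dropout rate is a fraction of the patients recruited. To have a target number left after losses, the target must be divided by the fraction retained. Multiplying the target by one plus the dropout rate applies the rate to the wrong base and always gives too few patients.

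If that happened here, three stated figures do not fit together: 60 per group, 20% dropout and 72 recruited. The total of 216 comes straight from this step. The protocol's own target of 60 would then be missed when dropout runs at the rate the protocol expects.

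**Working it through.** **Inputs, all from the sample size section unless marked**

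- Target before dropout: 60 per group
- Dropout: about 20%
- Recruited: 72 per group, 216 in total
- Two-sided α 0.05, β 0.15 (power 85%), base size 46 per group
- Relief on active treatment 70%, difference 30 percentage points
- *Inferred:* placebo relief 70% − 30% = 40%, which the article does not state
- *Assumed:* the calculation compares one active dose with placebo, because the article does not name the comparison

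**1. Reproducing the plan's 72**

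| Route | Calculation | Result |
|---|---|---|
| Multiply 60 by (1 + d) | 60 × 1.20 | **72** |
| Divide 60 by (1 − d) | 60 / 0.80 | 75 |
| Multiply 46 by (1 + d) | 46 × 1.20 = 55.2 | 56 |
| Divide 46 by (1 − d) | 46 / 0.80 = 57.5 | 58 |

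Only the first route gives 72, and it does so exactly.

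**2. What 72 delivers**

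- Left per group at 20% dropout: 72 × 0.80 = 57.6, which is 2.4 short of 60.
- Left overall: 216 × 0.80 = 172.8 against 3 × 60 = 180, which is 7.2 short.
- Highest dropout at which 72 still leaves 60: 1 − 60/72 = 16.7%.
- Number that keeps 60 at 20% dropout: 75 per group, 3 × 75 = 225 in total, 9 more than 216.

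**3. Checking the base of 46**

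For 70% against 40%, with p̄ = 0.55:

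- Pooled variance: n = [1.960 × √(2 × 0.55 × 0.45) + 1.036 × √(0.70 × 0.30 + 0.40 × 0.60)]² / 0.30² = 47.8, so 48.
- Unpooled variance: n = (0.21 + 0.24) × (1.960 + 1.036)² / 0.09 = 44.9, so 45.

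The stated 46 lies between these two, within 2 patients of each, so the power step is not in dispute.

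**4. Effect on power**

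With the pooled formula, power = Φ{[0.30 × √n − 1.960 × √0.495] / √0.45} at two-sided 0.05:

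| n per group | Power |
|---|---|
| 57 | 90.7% |
| 58 | 91.2% |
| 60 | 92.1% |

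As an illustration only, splitting α between two dose-placebo comparisons (two-sided 0.025 each) gives 84.7% at 57, 85.4% at 58 and 86.7% at 60.

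**The case against.** The case for leaving the text alone has four parts.

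- **The dropout rate is only approximate.** The text says "Taking approximate dropouts of 20% into account" with that qualifier, and 16.7% is not far from 20%. But 72 is exactly 60 × 1.20, so 20% was the rate used and it was applied to the wrong base. The figure is not a loose rounding of 16.7%.
- **Not every dropout is lost to analysis.** Under the statistical analysis section, the full analysis set keeps treated participants with follow-up data and carries the last observation forward. VAS is recorded nightly, and a last visit is sought from those who withdraw. This stands in part: the shortfall falls mainly on the per-protocol set and on completers. Efficacy is also analysed in the per-protocol set, however, and a dropout allowance serves no purpose unless it leaves the 60 after losses.
- **The 60 is not a power requirement.** This stands. The power-based number is 46, and 72 recruited keeps 46 until dropout reaches 1 − 46/72 = 36%. No test or decision rule depends on the missing 2 to 3 patients.
- **The alternative of 75 is awkward.** This also stands. With blocks of six, 216 makes 36 full blocks but 225 makes 37.5, and recruitment began on 26 March 2019. It is a reason to prefer restating the figure over adding patients.

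**Conclusion.** The dropout step is wrong as written. At 20% dropout, 72 per group leaves 57.6 rather than 60, and the size consistent with the stated target and rate is 75 per group (225 in total). This rests only on figures in the sample size section and on the ordinary meaning of dropout as a share of those recruited.

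The practical effect is small: about 1 percentage point of power for the 30-point difference, which stays above the planned 85%. The power figures depend on the inferred 40% placebo rate and on a single active-versus-placebo comparison at two-sided 0.05. The trial is not shown to be underpowered by this error. It is a low-priority correction to the justification of the trial's size.

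**What to change.** Keep 216 and correct the dropout sentence. Suggested content: 72 randomised per group leaves 57 to 58 per group after 20% dropout, or 60 if dropout does not exceed 16.7%; with relief of 70% against an assumed 40%, one active dose against placebo, two-sided α 0.05, power is about 91%. The sponsor should confirm that the 40% and the named comparison are what the original calculation used.

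This costs one sentence and a slightly less favourable retained number, with no extra patients and no design change.

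If 60 per group after dropout is a firm requirement, recruit at least 75 per group (225), which is 9 more patients. Filling whole blocks of six would take this to 228 (38 blocks, 76 per group), which is 12 more. As recruitment has started, either increase should be made as a protocol amendment, and the total of 216 changed wherever it appears.

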### Statistical analysis

The full analysis set (FAS) includes all randomized participants who take at least one bag of ZHWFG and have follow-up data. If post-treatment follow-up data regarding the primary outcomes are missing, last observation carried forward method will be carried out to adjust for the missing data. Per-protocol set (PPS) includes patients in the FAS who comply with the protocol, are adherent to the assigned study medication, complete the visits and measurements, and have no other protocol violations. Efficacy analysis will be performed based on both FAS and PPS patients. Safety analyses include all randomized participants who take at least one bag of ZHWFG and have data for safety assessment.

An independent statistician will perform statistical analysis according to the statistical analysis plan using Statistical Analysis System (SAS) 9.4. Continuous variables will be expressed as mean (standard deviation) if the data are normally distributed, otherwise median (inter-quartile) alternatively. Categorical variables will be presented as frequency (percentage). Baseline analyses will be performed using analysis of variance or nonparametric tests for continuous variables, and chi-squared or Fisher’s exact tests for categorical variables, respectively. The primary outcomes will be analyzed using CMH-*χ*^2^ test with associated 95% confidence intervals. Time to cough resolution and relief will be analyzed using the Kaplan-Meier approach, and the difference across groups will be compared using the log-rank test. Changes from baseline to post-treatment in CSS, TCM syndrome scores, VAS, and CQLQ will be analyzed using analysis of covariance with associated 95% confidence intervals. A two-sided *P* value of 0.05 or less is considered statistically significant.

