### Concomitant treatments and forbidden medication

Medications applied to treat the underlying diseases, such as diabetic mellitus and hypertension, are permitted. However, new use of angiotensin-converting-enzyme inhibitors for hypertension is not permitted. Any Western medication or other Chinese medicinal therapy which can relieve cough is prohibited during the study. Additionally, antibiotics are not allowed in this study. If the participants take any forbidden medication, they will be withdrawn. Any medication used in this study must be documented in detail in case report forms (CRFs), including name, dose, dosage regimen, indication, and treatment period.

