### Withdrawal and termination criteria

Participants may discontinue the study prematurely at any time for any reason. The investigators will be entitled to withdraw any participant because patients develop SAE or allergic reaction, experience condition worsening, loss to follow-up, or take forbidden medications.

The National Pharmaceutical Supervisory and Administrative Department can terminate the whole study for any reason. The investigators may terminate or suspend the study due to SAE, poor efficacy, or significant deviation from the protocol during the study. The sponsors can also terminate the study because of management issues or funding problems.

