### Outcome measures

#### Primary outcomes

Cough resolution rate: the proportion of patients whose cough is completely resolved.

Cough severity will be self-rated using a validated continuous horizontal 100-mm visual analog scale (VAS), with 0 indicating “no cough” and 100 indicating “worst possible cough” [11]. VAS value of the past 24 h will be evaluated every night at about 8:00 pm during treatment. Complete resolution of cough is defined as a reduction of VAS value to less than 17 mm [12]. Cough resolution rate across groups will be compared at days 7 and 14.
2.Cough relief rate: proportion of patients who achieve cough relief.

Cough relief is defined as a reduction of VAS value by 50% or more from the baseline. Cough relief rate across groups will be compared at days 7 and 14.

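### Carrying the last VAS forward whatever the reason for missingness can count participants withdrawn for taking cough medicine as responders on both primary outcomes

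*Protocol article*

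**What the plan says.** All references are to the protocol article.

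- **Missing data.** Under Statistical analysis, where post-treatment primary-outcome data are missing, "last observation carried forward method will be carried out to adjust for the missing data". No other missing-data rule is stated. Efficacy is analysed in the full analysis set (FAS) and the per-protocol set (PPS).
- **Forbidden treatment.** Under Concomitant treatments and forbidden medication: "Any Western medication or other Chinese medicinal therapy which can relieve cough is prohibited during the study". Antibiotics are barred too. The consequence is: "If the participants take any forbidden medication, they will be withdrawn".
- **Discretionary withdrawal.** Under Withdrawal and termination criteria, the grounds on which investigators may withdraw participants include that they "experience condition worsening, loss to follow-up, or take forbidden medications".
- **Primary outcomes.** For relief: "Cough relief is defined as a reduction of VAS value by 50% or more from the baseline". For resolution: "Complete resolution of cough is defined as a reduction of VAS value to less than 17 mm". Both are compared at days 7 and 14. The data come from a diary: "VAS value of the past 24 h will be evaluated every night at about 8:00 pm during treatment".
- **After withdrawal.** Data collection and management plans an attempt, subject to consent, at one final visit to obtain outcome data.

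The article nowhere classes a participant withdrawn for forbidden medication or worsening as a non-responder.

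**The concern.** Some of the missing data arise from treatment failure. A participant who needs another cough remedy has, for the question this trial asks, not been helped enough by the study granules. That participant is withdrawn, and the day-7 or day-14 result becomes the last available VAS. Because success is a cut-off on a single evening's value, that one reading decides the classification.

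Two routes lead to a wrong success:

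1. The last diary value already met the 50% or the 17 mm rule on a good evening before withdrawal.
2. The last value was recorded after the forbidden medicine and reflects its effect.

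The second route makes forbidden medication the main problem. A participant withdrawn for worsening will usually have a high last VAS, which LOCF records as failure. The exception is a partial relapse. With a baseline of 80 mm, for instance, a rebound from 30 to 40 mm is a worsening that still satisfies the 50% rule.

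LOCF can also err the other way. The Background describes the illness as usually self-limiting, so an early leaver is held near baseline although later improvement was likely.

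At stake are the two primary response rates and, where the arms differ in withdrawal or in the leavers' last values, the treatment difference. The sample size section allows for about 20% dropout.

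**Working it through.** **Inputs from the article (Sample size calculation):** relief 70% on active; difference 30 points, so placebo is taken as 40%; two-sided alpha 0.05; power 85%; 46 per group, raised to 60 and then to 72; dropout about 20%.

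**Inputs assumed, because the article does not give them:** f, the share of leavers whose last VAS meets the relief rule, and any difference in withdrawal between arms.

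**Step 1. The plan's own figure.** For 70% v 40%, the normal-approximation sample size is 47.8 with pooled variance (48 per group) and 44.9 with unpooled variance (45 per group). The stated 46 lies between them, so the planning values are read correctly.

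**Step 2. Effect of LOCF under the planned effect.** Arm rate = (1 − d) × completer rate + d × f, where d is the dropout share. Counting every leaver as a failure sets f = 0. With d = 0.20 (0.20 × 72 = 14.4 per arm), completers at 70% v 40% and n = 72:

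| f active / placebo | Active | Placebo | Difference | Power |
|---|---|---|---|---|
| 0 / 0 | 56% | 32% | 24 | 83.4% |
| 0.2 / 0.2 | 60% | 36% | 24 | 82.9% |
| 0.5 / 0.5 | 66% | 42% | 24 | 83.1% |
| 0.5 / 0.2 | 66% | 36% | 30 | 95.7% |
| 0.2 / 0.5 | 60% | 42% | 18 | 58.1% |
| 0.7 / 0.4 | 70% | 40% | 30 | 95.9% |

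Equal f raises both rates by 4 to 10 points and leaves the difference unchanged. Unequal f moves the difference by 0.20 × (0.5 − 0.2) = 6 points, in either direction.

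**Step 3. No true effect, unequal withdrawal.** Let the true success rate be 40% in both arms, all leavers be true failures, f be the same in both arms, and n = 72. The analysed rate is 0.40 + d × f. The rejection probability is Φ(δ/SE − 1.96) + Φ(−δ/SE − 1.96), where δ is the difference in analysed rates.

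- 20% v 10% withdrawal, f = 0.3: 46% v 43%, δ = 3 points, SE = 0.0828, rejection 6.5%.
- 20% v 10% withdrawal, f = 0.5: 50% v 45%, δ = 5 points, SE = 0.0831, rejection 9.2%.
- 30% v 10% withdrawal, f = 0.3 to 0.5: δ = 6 to 10 points, rejection 11.2% to 22.6%.
- 20% v 20% withdrawal: δ = 0, rejection 5%.

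If placebo has the higher withdrawal, the sign reverses. For example, if 5% of active and 15% of placebo participants take forbidden medicine and half show a low last VAS, the shift is (0.05 − 0.15) × 0.5 = −5 points, against the active arm.

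**The case against.** **Safeguards exist.** The article plans an attempted final visit after withdrawal and a PPS analysis. Neither changes the FAS rule. The visit depends on consent, and a value obtained after a cough remedy may reflect that remedy. The PPS drops protocol violators and does not count them as failures.

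**The bias may be nil or conservative.** This stands. Equal withdrawal and equal last-day response leave the difference untouched, and more remedy use on placebo would shrink it. If the granules do nothing, the article offers no reason why withdrawal should differ between arms. A reader might infer that LOCF favours the active arms; the documents do not support that.

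**A larger error rate could be quoted.** Assuming that 50% of active and 20% of placebo leavers meet the rule at 20% dropout gives a 6-point shift and about 11% rejection at n = 72. Nothing in the documents explains such a gap under no effect, so it should not be the headline.

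**LOCF is reasonable for an isolated diary gap.** This also stands. Carrying one evening forward by one day does little harm, and scoring every missing day-7 or day-14 entry as failure would penalise someone almost free of cough the evening before. The remedy should therefore depend on the reason for missingness.

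**The time-to-event analyses.** A reader might infer the same fault there. The article says only that "Time to cough resolution and relief will be analyzed using the Kaplan-Meier approach", with a log-rank comparison. It states no censoring rule, and such detail commonly sits in the analysis plan, so no finding follows.

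**The unseen analysis plan may refine the rule.** It may, but the article itself fixes LOCF for the primary outcomes, so this is a stated choice and not an omission.

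**Conclusion.** The point holds in a limited form. As written, the FAS rule can classify a participant withdrawn for taking a cough remedy as relieved or resolved, and less often one withdrawn for worsening. The mechanism follows directly from the article's own rules. Its size does not: the direction is unknown, the bias in the difference may be zero, and the illustrative 3 to 5 points (rejection about 6.5% to 9% against a nominal 5%) rests on an assumed 20% v 10% withdrawal and on 30% to 50% of leavers meeting the rule. The absolute response rates are more exposed than the difference, since equal behaviour across arms still inflates them.

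A reader might also make something of the fact that withdrawal for forbidden medication is mandatory in one section and at the investigators' discretion in another. That is a separate drafting matter, and this point does not depend on it.

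**What to change.** In the primary FAS analysis:

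1. Count a participant withdrawn for forbidden cough medication or for worsening before day 7 or day 14 as a non-responder at that day, disregarding any VAS recorded after the forbidden medication.
2. Handle other missing day-7 or day-14 values, including isolated diary gaps, by multiple imputation from the daily diary.
3. Report LOCF, and all missing values as non-response, as sensitivity analyses.

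**Cost.** Response rates and power fall somewhat. At the extreme, with all 20% of dropouts counted as failures, 70% v 40% becomes 56% v 32%. The difference falls from 30 to 24 points, and power at 72 per arm falls from about 96% to about 83%, close to the planned 85%. The actual loss should be smaller, because only withdrawals for the two named reasons are set to failure. The Ethics and dissemination section requires changes to analyses to be resubmitted and approved. Recruitment had already begun, so the change should be made and dated before unblinding.

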**Inclusion criteria**	
1. Diagnosis of postinfectious cough	
2. Wind-cold invading lungs syndrome in traditional Chinese medicine Zheng	
3. Cough duration of 3–6 weeks	
4.Baseline cough visual analog scale of 60 mm or more	
5. Aged 18 to 65 years old	
6. Voluntarily provide written and informed consent	

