### Randomization and blinding

Randomization sequence will be created by an independent statistician. Randomization will be carried out in blocks of six using Statistical Analysis System. Participants will be stratified according to study center and randomly assigned in a 1:1:1 ratio. Active and placebo granules will be identical in terms of outer package, labeling, and outer appearance of the medication packs. Random assignment sequence is concealed on a sealed scratch card in each study center to be revealed only when a medical emergency occurs. A research assistant will enroll participants and assign them to interventions. Investigators, participants, and biostatisticians will be masked to treatment assignments during the whole treatment duration. Unblinding is permissible only when a serious adverse event (SAE) or emergency rescue occurs.

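### The named primary test does not adjust for continuous baseline VAS, although resolution is an absolute cut-off that is harder to reach from a higher entry value: a loss of precision, not a bias

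*Protocol article*

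**What the plan says.** The Statistical analysis section of the protocol article fixes the primary method: "The primary outcomes will be analyzed using CMH" (the sentence continues with the chi-square test and 95% confidence intervals). It names no strata and no covariates.

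The two primary outcomes are dichotomies of the same 100-mm cough scale, compared at days 7 and 14 (Primary outcomes):

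- Resolution is absolute: "Complete resolution of cough is defined as a reduction of VAS value to less than 17 mm".
- Relief is relative: "Cough relief is defined as a reduction of VAS value by 50% or more from the baseline".

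Table 3 sets the entry condition: "Baseline cough visual analog scale of 60 mm or more". The scale ends at 100 mm, so baseline values lie between 60 and 100 mm. On allocation, Randomization and blinding says: "Participants will be stratified according to study center and randomly assigned in a 1:1:1 ratio".

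Changes in continuous scores, including change in VAS, "will be analyzed using analysis of covariance with associated 95% confidence intervals". The covariates of that analysis are not listed. Further detail is deferred: "An independent statistician will perform statistical analysis according to the statistical analysis plan". That plan is not shown.

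**The concern.** The hurdle for resolution depends on where the patient starts, and the starting value is recorded for everyone because relief is calculated from it. If baseline VAS predicts resolution, a test that leaves it out carries avoidable variation. Power is then lower than the same patients could give, and a chance imbalance in baseline VAS between arms shifts the observed resolution rates without correction.

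This does not depend on what the unseen analysis plan may add. The article itself chooses the test, and a CMH test can use VAS only if it is cut into categories that serve as strata, which the article does not mention. The choice is also uneven. Change in VAS, a secondary outcome, is given a method built for covariates, while the primary outcomes derived from the same scale are not.

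Resolution is the more exposed of the two. The sample size section works from the relief rate only, so no power figure is stated for resolution.

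**Working it through.** **1. The plan's own figure.** Inputs from Sample size calculation: 70% relief on active treatment, a 30-point difference (so 40% on placebo), two-sided alpha 0.05, beta 0.15, stated result 46 per group.

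- Unpooled variance: n = (1.960 + 1.036)² × (0.70×0.30 + 0.40×0.60) / 0.30² = 8.98 × 0.45 / 0.09 = 44.9, so 45.
- Pooled variance: n = [1.960×√(2×0.55×0.45) + 1.036×√0.45]² / 0.09 = (1.379 + 0.695)² / 0.09 = 47.8, so 48.

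The stated 46 lies between the two and is reproduced closely enough. Power for 70% versus 40% is 0.84 at 46 per group, 0.92 at 60 and 0.96 at 72. All of this concerns relief with an unadjusted test.

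**2. The hurdle by entry value.**

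| Baseline VAS | Fall needed for resolution (<17 mm) | As % of baseline | Fall needed for relief | As % |
|---|---|---|---|---|
| 60 mm | more than 43 mm | 71.7% | 30 mm | 50% |
| 80 mm | more than 63 mm | 78.8% | 40 mm | 50% |
| 100 mm | more than 83 mm | 83.0% | 50 mm | 50% |

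For resolution the hurdle rises on both scales, but by only 83.0 − 71.7 = 11.3 percentage points on the relative scale. For relief the relative hurdle is constant.

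**3. What adjustment could gain.** The article gives neither a baseline-outcome correlation nor a centre variance, so two sets of simulations span a range of assumptions.

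*Set A:* 58 per arm (72 × 0.8 = 57.6), truncated-normal baseline on 60 to 100 mm, day-14 VAS linear in baseline, SD 20 to 28 mm, effect 14 mm, assumed baseline/day-14 correlation 0.15 to 0.53, 1,500 trials per setting. The last two rows are at correlations 0.38 and 0.53.

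| Resolution: unadjusted / adjusted | Gain (points) | Relief: unadjusted / adjusted | Gain (points) |
|---|---|---|---|
| 0.511 / 0.518 | 0.7 | 0.574 / 0.576 | 0.2 |
| 0.474 / 0.503 | 2.9 | 0.554 / 0.565 | 1.1 |
| 0.705 / 0.740 | 3.5 | 0.821 / 0.841 | 2.0 |
| 0.675 / 0.741 | 6.6 | 0.763 / 0.825 | 6.2 |

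*Set B:* resolution only, 60 per arm, six centres, uniform baseline on 60 to 100 mm, 600 trials per setting. Centre-stratified CMH is compared with a logistic likelihood-ratio test adjusting for baseline and centre.

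| Assumed course of VAS | Correlation of resolution with baseline | Centre effect | CMH | Logistic | Gain (points) |
|---|---|---|---|---|---|
| Falls in proportion to baseline | about −0.1 | none | 0.863 | 0.872 | 0.9 |
| Falls in proportion to baseline | about −0.1 | present | 0.807 | 0.818 | 1.1 |
| Falls by an absolute amount | about −0.4 | none | 0.690 | 0.803 | 11.3 |
| Falls by an absolute amount | about −0.4 | present | 0.688 | 0.772 | 8.4 |

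**4. Validity.** With no treatment effect in set B, the CMH test rejected in 0.03 to 0.05 of trials, stratified or not, so its level is held. The logistic likelihood-ratio test rejected in 0.05 to 0.06, so its gain is slightly overstated. The Monte Carlo standard error of a set B power figure is √(p(1−p)/600), about 1.4 to 1.9 points. The gains near 1 point are therefore not clearly different from none.

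**The case against.** The strongest reply is that nothing here is invalid. Randomisation balances baseline VAS in expectation, the error rate of the CMH test already allows for chance imbalance, and CMH is a standard choice for binary outcomes under centre-stratified randomisation. That stands, and it limits the point to efficiency.

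The size is also uncertain. No passage relates baseline VAS to resolution, entry is truncated at 60 mm, and if cough falls in proportion to its starting level the gain is about 1 point. A reader might infer from the absolute cut-off that resolution is strongly tied to starting VAS. The documents give no figure for this, and the tie could be weak.

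Relief, which drives the sample size, is already scaled to the patient's own baseline. At the planned 70% versus 40% it has power of about 0.92 with 60 per group. The simulated effects in set A are smaller than that, so the room for gain on relief at the design point is less than the table suggests.

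A reader might also infer that the time-to-event analyses ignore centre, because the article says only that "the difference across groups will be compared using the log-rank test". This is not supported. The article does not say whether that test is stratified, and strata are commonly left to the analysis plan to which it refers.

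What survives is narrow. The primary method is stated, it does not use continuous baseline VAS, and a method that does is available from data already collected.

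**Conclusion.** The point holds as a matter of precision. The named primary test leaves out the entry value of the scale that defines both primary outcomes, and for resolution the hurdle rises with that value. Under assumed baseline-outcome relations, adjustment adds roughly 1 to 11 points of power for resolution: about 1 if VAS falls proportionally, and 8 to 11 if it falls by an absolute amount. For relief it adds from almost nothing to about 6 points. The documents do not settle which assumption applies.

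The results do not support calling the CMH analysis biased or anti-conservative, and the point does not weigh equally on both primary outcomes. It matters most for resolution, for which the article states no power.

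**What to change.** Before unblinding, specify for the primary outcomes, and above all for resolution, a logistic regression with treatment (three arms), baseline VAS as a continuous covariate, and centre. Report the standardised risk difference with its 95% confidence interval at each planned time point. State the test and variance estimator in advance, since the likelihood-ratio test ran slightly above its nominal level in simulation. Keep the CMH test, stratified by centre, as a sensitivity analysis.

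The cost is wording in the analysis plan and the matching sentence of the protocol. No extra patients, visits or measurements are needed. Under Ethics and dissemination, important changes to the analyses go back to the ethics committee, so the change should be submitted there and dated.
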